#### Process evaluation

The aims of the process evaluation were to facilitate the intervention development process and to identify barriers and facilitators in the implementation process. To help facilitate intervention development, the process evaluation was designed based on formative process evaluation principles [37, 38]. The process evaluation was carried out using an electronic survey to the 17 school principals from the cases selected for development in June 2013 and focus group interviews with the 7 final case teams were conducted in April 2014, and will be conducted in spring 2016. The survey included questions about rules and policies regarding recess, PA, outdoor teaching and activities outside school hours. Furthermore the schools were asked about their initial plans and expectations towards the process.

The focus group interviews included between 5 and 10 members of the final seven case teams and the interviews focused on the case teams’ experiences during the project development process and their expectations for the coming implementation process. The interviews took place at the intervention schools and lasted approximately 90 min. The second focus group interviews with the case teams in spring 2016 will provide insights to the organizational changes implemented in each of the cases, as well as the intervention implementation process.

#### Post-intervention user-evaluation

The aim of the in-depth post-intervention user-evaluation is to explore how, and by whom, the new elements in the schoolyard are used, within and outside of school hours. The study will also explore how students perceive the organizational and physical changes.

### Data analysis

#### Exploratory study

Upon completion of the exploratory study, field notes, interview transcripts and photos were ordered with the explicit purpose of identifying barriers influencing engagement in recess PA across the cases [39]. The data was coded and arranged under headings derived from the social-ecological model distinguishing natural, social, physical and organizational barriers [40].

#### Effect evaluation

The effect of the schoolyard interventions on PA will be assessed by calculating the difference in the objectively measured average activity level (in counts per minute, CPM) during recess in the schoolyard, before and after the intervention (Δ average CPM during recess) using multilevel modelling to account for the nested structure of the data (*i.e.* time points, students, class, school). The analyses will be adjusted for overall activity levels, age, gender and parents’ socio-economic status. Furthermore, analyses of changes in the proportion of time in sedentary, light and MVPA in the schoolyard will be calculated to exemplify change in activity levels post the interventions. To increase generalizability of the findings, the objectively measured average activity level at the intervention schools will be compared to objectively measure average activity levels of students during recess for approximately 40 other Danish schools. This data is or will be available from other studies conducted by our university department.

The analysis of the secondary outcomes will be more exploratory requiring new methods to clean and prepare useful variable based on combined accelerometer and GPS data. Examples of secondary outcomes are: areas generating high level of activity (CPM or MVPA) in the schoolyard, areas of the schoolyard most likely to encourage MVPA for different groups of students (boys/girls, high/low activity groups, age-groups), exploring routes of activity in the schoolyard.

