#### Effect evaluation

The aim of the effect evaluation is to examine the effect of the tailored interventions in each of the cases on student’s PA and movement patterns during recess. Movement pattern is defined as PA intensity levels at specific geographic locations. The primary outcome is the difference in the objectively measured average activity level (in counts per minute, CPM) during recess in the schoolyard, before and after the intervention. The secondary outcomes are more exploratory examining intervention effects for the least active students, and exploring the change in behavior in specific areas of the schoolyard.

Baseline data were collected April to July 2014, and follow-up data will be collected in the same period (April to July) in 2016. A combination of accelerometers, GPS and geographic information system (GIS) was used to assess behavior changes in time and space in each of the seven cases. Objective PA was recorded as an activity-count every 15 s using the ActiGraph accelerometer model GT3X. The ActiGraph accelerometer has previously been recognized to provide acceptable validity and reliability for measuring children’s activity levels and energy expenditure [34, 35]. The students’ locations were measured every 15 s using QStarz BT-Q1000xt GPS trackers. The Qstarz GPS units have a median dynamic positional error of 2.9 m in real-world conditions, within various urban environments and during different modes of transport [36]. The schoolyards were mapped in detail using ArcGIS 10.2 and the total schoolyard area was calculated. During the week of measurements all participants completed an electronic survey, inquiring about self-reported PA, neighborhood and school experiences, and background characteristics.

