### Design

The design is quasi-experimental, using existing data for comparison. Over the last decade the majority of published recess intervention studies have used randomized control trials (RCT) or quasi-experimental designs [18–20, 41–43]. In contrast to the RCT design we purposefully selected the cases that were to receive an intervention, and will compare the results with data from other cases that were also not randomly selected. In principle, not using an RCT design reduces the internal validity of a study: the starting point for the intervention cases and the comparison cases is not necessarily the same and potential changes might not be (entirely) explained by the intervention. Comparing our results to objectively measured PA levels of students from up to 40 other Danish schools makes it possible to assess if changes occurring over time were the result of temporal trends or the intervention. As the comparison cases were not selected randomly, potential differences between intervention and comparison outcomes are at some risk for confounding or bias.

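### The primary effect is an uncontrolled 2014-to-2016 change, and the planned comparison of activity levels with about 40 other schools cannot separate intervention from trend as the Discussion says

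*Protocol article*

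**What the plan says.** Three places in the Protocol article bear on this point.

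**Method, Data collection and measurements, Effect evaluation.** "The primary outcome is the difference in the objectively measured average activity level (in counts per minute, CPM) during recess in the schoolyard", taken before and after the intervention. Baseline ran from April to July 2014, and follow-up is planned for the same months of 2016.

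**Method, Data analysis, Effect evaluation.** The effect is the difference "before and after the intervention (Δ average CPM during recess) using multilevel modelling to account for the nested structure of the data". The levels named are "time points, students, class, school". On covariates: "The analyses will be adjusted for overall activity levels, age, gender and parents’ socio-economic status". The external schools come in afterwards, with their own purpose and their own quantity: "To increase generalizability of the findings, the objectively measured average activity level at the intervention schools will be compared" with average recess levels at roughly 40 other Danish schools. On their source: "This data is or will be available from other studies conducted by our university department".

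**Discussion, Design.** Setting the results against activity levels at up to 40 other schools "makes it possible to assess if changes occurring over time were the result of temporal trends or the intervention". The same paragraph accepts that non-random selection weakens internal validity, that intervention and comparison schools may start from different points, and that the comparison carries some risk of confounding.

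**The concern.** The analysis section and the Discussion give the same comparison two different jobs. In the analysis section it supports generalizability and is made on levels. In the Discussion it tells a temporal trend from an intervention effect. The second job needs the change at comparison schools over a matching period, set against the change at intervention schools. The analysis section does not describe that contrast.

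At stake is how the primary result may be read. Two years separate the waves. A shift in recess activity common to Danish schools, or a change in school policy, would be counted as intervention effect or would hide one. A reader who relies on the Discussion would believe this had been dealt with.

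**Working it through.** The article states no figure on this point, so there is nothing to reproduce. The check is what each contrast estimates.

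**Notation** (mean recess CPM):
- D: intervention effect
- T: two-year drift at the intervention schools that remains after the planned adjustment
- Tc: the same drift at the comparison schools
- G: baseline gap, intervention minus comparison
- M: baseline mean at the comparison schools

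**Cell means**
- Comparison, 2014: M
- Comparison, 2016: M + Tc
- Intervention, 2014: M + G
- Intervention, 2016: M + G + T + D

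**Contrasts**
1. Before/after at the intervention schools (the stated primary effect): (M + G + T + D) − (M + G) = **D + T**.
2. Levels in 2016, intervention minus comparison: (M + G + T + D) − (M + Tc) = **D + G + (T − Tc)**.
3. Intervention level in 2016 against comparison data pooled equally over both years (possible, since the article does not date those data): (M + G + T + D) − (M + Tc/2) = **D + G + T − Tc/2**.
4. Difference in changes: (D + T) − Tc = **D + (T − Tc)**.

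**Illustration.** The article gives no CPM values, so D, T, Tc and G below are assumptions chosen only to show direction.

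| D | T | Tc | G | 1. Before/after | 2. Levels 2016 | 3. Level vs pooled | 4. Difference in changes |
|---|---|---|---|---|---|---|---|
| 0 | +50 | +50 | 0 | +50 | 0 | +25 | 0 |
| 0 | −50 | −50 | +60 | −50 | +60 | +35 | 0 |
| +50 | −50 | −50 | +60 | 0 | +110 | +85 | +50 |
| 0 | −50 | −20 | +60 | −50 | +30 | +20 | −30 |

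**Reading the rows**
- Row 1: with no effect, the primary estimate reports the whole drift. The 2016 level contrast is right here only because G is zero.
- Row 2: with no effect and a baseline gap, the primary estimate and both level contrasts are wrong, and the primary estimate has the opposite sign to the level contrasts.
- Row 3: a real effect disappears from the primary estimate and is more than doubled in the 2016 level contrast.
- Row 4: the difference in changes also fails when the two groups drift differently. It rests on T = Tc.

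**What the planned covariates and timing remove.** Season is matched in contrast 1, because both waves run from April to July. Adjustment for age can take out part of ageing, and adjustment for overall activity can take out some general drift. Neither is a concurrent control. Drift specific to recess, from calendar time or school policy, stays in T.

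**Can G be taken as zero?** No. The intervention cases were picked by competition, the comparison schools were not randomly selected, and the Discussion itself says that the two groups need not start alike.

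**The case against.** The strongest defence has three parts.

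*The limitation is disclosed.* The Discussion admits reduced internal validity and possible confounding. This stands as a description of selection bias. It does not remove the separate statement that trends can be told apart from the intervention.

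*A contrast of changes may be intended.* The Discussion speaks of changes over time, and the analysis section does not rule out comparing levels at both time points. The dates and grades of the other schools' data, and the exact model terms, may sit in a fuller plan. This also stands, so leaving those details out is not the finding. The finding is that the article itself fixes the estimator and the purpose of the comparison, and then claims a property that a contrast of levels lacks.

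*The covariates and timing already limit drift.* This stands in part, as set out in the working.

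Some stronger readings are tempting but are not supported:
- A reader might infer that season biases the primary contrast. The matched months rule that out as a general charge.
- A reader might infer that every kind of two-year drift passes straight into the estimate. That ignores the planned adjustment for age and overall activity.
- A reader might infer that the outcome differs between groups, because the primary outcome is tied to the schoolyard while the comparison refers only to recess. The analysis section uses the shorter form for the intervention-school outcome as well, so condensed wording is an equally good explanation.
- A reader might want a false-positive rate for a given drift. It would need an SD of change, a retention rate and a between-school variance, and the article gives none of them.

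**Conclusion.** The concern holds in this form. The primary effect is an uncontrolled before/after change and estimates D + T. The planned comparison of levels estimates D + G + (T − Tc) at best, so it cannot support the trend-separation statement in the Discussion. The size of the bias in the primary estimate is T itself, CPM for CPM and in either direction, whatever the standard error. Its value cannot be derived from the article.

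The algebra needs no assumed numbers. The conclusion rests on reading the comparison as the analysis section words it, and on G not being known to be zero, which the Discussion concedes. It would be wrong to conclude that the external schools can never help. If some were measured around both 2014 and 2016, a contrast of changes is available and would remove any drift that the two groups share.

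**What to change.** Keep the primary outcome as stated. Replacing it with CPM over all timetabled recess would change what is being estimated, and this point does not require that.

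In Data analysis, Effect evaluation:
- State that the comparison with other schools serves to separate the intervention effect from temporal trend.
- Specify it as a contrast of changes: a group-by-time term in the multilevel model, with intervention and comparison students analysed together.
- Limit that contrast to comparison schools measured around both 2014 and 2016, in similar months and grades, with recess CPM derived in the same way in both groups.
- Use schools with a single wave descriptively only.
- State that the contrast assumes similar drift in the two groups.

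If no such two-wave data exist, remove the trend-separation statement from Discussion, Design, and report the primary result as an uncontrolled before/after change.

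**Cost.** The work is plan wording plus harmonisation of data that are, or are still to become, available from other studies. The confidence interval will be somewhat wider: for independent groups, Var(difference in changes) = Var(change, intervention) + Var(change, comparison), and the second term is new. How much wider cannot be given without variance figures. No new measurement at the intervention schools is needed.

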#### Process evaluation

A descriptive analysis of data from the pre-intervention electronic survey was conducted to identify the organizational structure at the cases regarding recess and schoolyards policies, rules and practices prior to the intervention. The pre- and post-intervention focus group data will be analyzed as a whole using a thematic analysis strategy [29, 30]. Relevant themes across cases related to how the process was experienced by the case teams and school principals in the different phases will be extracted to identify barriers and facilitators.

#### Post-intervention user-evaluation

Upon completion of the post-intervention user evaluation, field notes, interview transcripts and photos will be analyzed using a thematic analysis strategy [29, 30]. Themes will be developed through a coding and re-coding process in order to identify commonalities and divergences in how the students perceive and use their schoolyard within and between cases [39].

## Discussion

The aim of this paper was to present the study design, case selection, intervention development and measurements of the Activating Schoolyards study.

Tailored interventions that consist of changes to the physical schoolyard environment as well as the organizational context will be implemented in seven cases. As there are many different factors that can influence the result of this type of interventions, evaluating the effect and generalizing findings to other situations is rather complex, and requires a multitude of methods. The participatory approach and case selection strategy make the study design novel in many ways, providing a series of benefits, but also some challenges that will be discussed in the next sections.

### Design

The design is quasi-experimental, using existing data for comparison. Over the last decade the majority of published recess intervention studies have used randomized control trials (RCT) or quasi-experimental designs [18–20, 41–43]. In contrast to the RCT design we purposefully selected the cases that were to receive an intervention, and will compare the results with data from other cases that were also not randomly selected. In principle, not using an RCT design reduces the internal validity of a study: the starting point for the intervention cases and the comparison cases is not necessarily the same and potential changes might not be (entirely) explained by the intervention. Comparing our results to objectively measured PA levels of students from up to 40 other Danish schools makes it possible to assess if changes occurring over time were the result of temporal trends or the intervention. As the comparison cases were not selected randomly, potential differences between intervention and comparison outcomes are at some risk for confounding or bias.

### Case selection

The main reason for purposefully selecting the intervention cases was to increase the external validity of our results. Our intention with the case selection strategy and intervention development was to optimize the conditions needed to create a highly motivating and involving process [23, 24]. With the use of this selection strategy, the intervention development process, and the substantial amount of funding allocated to the cases, we aimed at making our cases ‘critical cases’ [44]. Theoretically, this means that if we do not find an effect in the current cases, we will not find an effect using this process elsewhere [44]. However, even if the interventions are successful, we fully acknowledge that it will be difficult to implement this type of intervention on a large scale as this would require many resources. Nonetheless, we do think that evaluating the effect and exploring the change in behavior in relation to specific intervention elements in the schoolyard will lead to recommendations for schools undergoing schoolyard renovations at some point in the future. The division of students into groups with different activity levels gives us the opportunity to explore whether specific designs or constructions serve different groups better than other in the recess domain.

Reflecting upon our case selection strategy, we anticipated that the participating schools were highly motivated, and that the competition fostered many original ideas that had strong local support. Even though only seven cases were selected for realization, we expect that some of 106 schools that submitted a vision will, in some way, continue developing their schoolyard; just by entering the competition thoughts and processes were set in motion. Results from the evaluation of another project with a similar form of recruitment by competition point to this [45].

On a more critical note, we should mention that we as researchers only had an advisory role in the selection of the seven cases. The evaluation panel appointed by the Partnership behind the Activating Schoolyards Campaign made the final decision and even though clear selection criteria were set, personal preferences and interests other than selecting the most appropriate cases seen from a research point of view might have played a role in the case selection.

### Development of interventions

During the intervention development phase principles of Community-Based Participatory Research were used to develop tailored interventions. This approach has proven to be an effective and viable approach for addressing social and cultural health disparities in community-based interventions [27]. Based on our previous experiences with schoolyard interventions, we learned that tailoring an intervention to local needs and wishes, building on local engagement, was crucial to the success of the intervention [24]. A consequence of this participatory approach was the diversity in the intervention development process and the driving force behind the ideas. In line with a participatory bottom-up approach it was up to the schools to define their case teams, resulting in a variation in the representatives involved. In some cases one or two teachers were in charge, in other a school principal, in a few cases parents, and sometimes planners from a municipality. Also the extent of student involvement varied. All case teams received similar inputs from researchers to help develop their idea.

### Measurements

Using the mixed methods design including qualitative and quantitative methods is a strength, with the different types of data complementing each other [46]. Data collected in the first exploratory study were, apart from being used by the case teams to help develop the interventions, also used to develop the student questionnaire in the effect evaluation. The results from the effect evaluation will be put into perspective using the data from the post-intervention user-evaluation. A process evaluation with several data collection moments will shed light on factors influencing the implementation of the interventions. These results will help understand and explain the results of effect analysis.

A novel aspect of our study is using the combination of accelerometer, GPS and GIS in the effect evaluation to objectively determine where and how active the students are in the schoolyard, before and after the intervention. This type of data has to our knowledge, not been used before in longitudinal studies to evaluate schoolyard interventions [19, 20]. A number of cross-sectional studies have used similar measures to look at how schoolyard environments influence the activity patterns and intensity levels [47–50].

The combination of accelerometer and GPS is relatively invasive for participants, and this might be reflected in the relatively low participation rate (52 %). Compared to earlier studies using the systematic observation method SOPLAY [25, 51, 52], our method has the added advantage that each individual is identifiable, which means that it is possible to adjust the analyses for the overall PA level of the individual student as well as other personal characteristics [53]. Additionally, the combination of accelerometer, GPS and GIS facilitates comparing activity levels across different locations with different features, something that is not possible in studies using SOPLAY [25]. Another strength of mixing these methods is the opportunity to divide students into groups based on their objectively measured activity level and *e.g.* focus on the least active students. Finally, these methods have the potential to assess if the change in activity in the schoolyard is ‘relocated’ activity (*i.e.* the same activity, but in a different location), or a true increase in activity.

